**Methods/design:**

We describe a single-center, parallel-design, double blind randomized, sham-controlled trial. Forty-five subjects with CKD undergoing HD will be randomized to a motor cortex (M1), a dorso lateral prefrontal cortex (DLPFC), or a sham group. A total of ten sessions will be administered to participants over 4 weeks using a monophasic continuous current with an intensity of 2 mA for 20 min. Participants will be evaluated at baseline, immediately after the tenth session, and at 1 week and 4 weeks of follow-up after the intervention. Pain, depression, functionality, and quality of life will be evaluated.

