### Sample size

Sample size was estimated based on statistical considerations for a parallel trial and on previous studies that have paired noninvasive stimulation with chronic pain syndromes [9, 10, 15]. No previous studies have reported results about tDCS using a visual analog scale (VAS) or numeric rating scale (NRS) in CKD. G-Power 3.1.9.2 was used to calculate sample size. VAS is a 0–10-point scale and will be used as the primary outcome. Sample size calculation assumed a significance of 0.05 and power of 0.80. Fregni suggested in previous studies that a mean reduction of 3 points in VAS for the group under active stimulation was expected in contrast to no improvement in the sham group [15]. Sample size was estimated based on the assumption of significance of 0.05, power of 95%, with 0.40 effect size. According to this methodology the sample size would be 36 participants. We decided to add nine more patients to prevent any reduction of power in case of patient dropout. Thus, 45 patients will be recruited and randomized into three groups of 15 patients each.

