### Outcome measures

This study will follow the outcome measures used in studies of multiday repetitive tDCS applied to the M1 or DLPFC to treat chronic pain and depression [17].

Data will be collected following assessments at baseline (week 2), immediately after the tenth day of intervention (week 6), and at 7- and 10-week follow-ups (Fig. 3). All evaluations will be performed by an experienced physical therapist blinded to group assignments. Socio-demographic and clinical characteristics will be collected from the participants and will include age, gender, ethnicity, marital status, level of education, income, time of HD, medication profile, and comorbidities.

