### Statistical analysis

Statistical analyses will use SPSS (v.19.0, Chicago, USA) and Graph Pad Prism 5. Clinical and sociodemographic characteristics (marital status, income, education, and ethnicity) will be described by means and standard deviations for continuous numeric parameters, and by frequency tables with 95% confidence intervals for categorical parameters. Chi-squared test will compare the distributions of categorical variables. Kruskal-Wallis test and ANOVA will compare differences in final values between groups.

The Shapiro-Wilk and Levene’s test will assess the normality of the distribution and homogeneity of variance of the data, respectively. Non-parametric tests will be used in case of non-normality distribution. Mauchly’s test of sphericity will be used to validate the correlation of the repeated measures and where the assumption of sphericity is violated, the Greenhouse-Geisser correction will be applied. The effects of stimulation on primary and secondary outcomes will be calculated using a mixed ANOVA model. The dependent variable will be the score of each outcome, and the independent fixed variables will be the time of treatment (baseline, tenth day, first follow-up, and second follow-up), the group of stimulation (active and sham), and the interaction term time vs group. Post-hoc comparisons will be carried out using Bonferroni correction for multiple comparisons.

Friedman test will be used for non-parametric data. Missing data will be treated by intention-to-treat analysis, taking into account the method of the last observation carried forward. Partial η^2^ will be calculated as measures of effect size in the ANOVA results (main effects and interaction effects). Partial η^2^ will be used to calculate the effect size, where η^2^ = 0.01 will be considered small, η^2^ = 0.06 moderate, and η^2^ = 0.14 large effect. Statistical significance will be set at *p* value less than 0.05.

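### Last observation carried forward, labelled intention-to-treat, is the only missing-data rule; it can bias the off-treatment contrasts in a direction that depends on when patients leave and what happens to pain afterwards

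*Protocol article*

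**What the plan says.** The rule is one sentence in the Statistical analysis section: "Missing data will be treated by intention-to-treat analysis, taking into account the method of the last observation carried forward". The article names no other method for missing data and no sensitivity analysis.

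The filled-in scores go into the main analysis: "The effects of stimulation on primary and secondary outcomes will be calculated using a mixed ANOVA model". Its time factor has four levels: "the time of treatment (baseline, tenth day, first follow-up, and second follow-up". The abstract places the two late visits "at 1 week and 4 weeks of follow-up after the intervention", and Outcome measures gives the study weeks: "immediately after the tenth day of intervention (week 6), and at 7- and 10-week follow-ups". The two descriptions agree (6 + 1 = 7 and 6 + 4 = 10), so weeks 7 and 10 are both off treatment. No outcome visit is listed between baseline and the tenth session.

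On the amount of missing data, Sample size says: "We decided to add nine more patients to prevent any reduction of power in case of patient dropout". This takes 36 patients to 45, or 15 per arm. The Discussion adds, without a rate, that adherence may suffer.

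**The concern.** The sentence merges two separate decisions. Analysing everyone in the arm to which they were randomised is sound. Single imputation by LOCF does not follow from it and brings an assumption of its own, that a score stays frozen after dropout.

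What is carried depends on when the patient leaves:

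- Last seen at week 7: the 1-week score stands in for the 4-week score.
- Last seen at week 6: the end-of-treatment score stands in for both follow-ups.
- Lost during treatment: baseline stands in for all three later visits and counts as no change.

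The follow-up visits show whether any benefit lasts once stimulation stops. The VAS asks about the previous 24 hours, so a week-6 rating carried to week 10 represents pain on a day four weeks later. If the effect fades, late losses make it look more durable than it is. If it persists, or patients leave early, LOCF understates it. The Discussion says the trial is to guide a larger multicentre study, so a distorted durability estimate would be passed on.

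**Working it through.** **Inputs from the protocol article.** 36 patients before and 45 after the dropout allowance; 15 per arm; visits at baseline and weeks 6, 7 and 10; an expected 3-point VAS reduction on active stimulation against none on sham (Sample size).

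**Inputs assumed, because the article does not give them.** The share missing at week 10, when patients leave, the course of pain after treatment, the VAS standard deviation (2 points) and the correlation between visits (0.5).

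**The plan's own figure.** The allowance is 9/45 = 0.20, and 36/(1 − 0.20) = 45, so the final size is consistent with 20% dropout. The figure of 36 can be reproduced for a three-group by four-visit interaction with effect size 0.40, 95% power and zero correlation between visits (power 0.957). The article states neither the test nor the correlation, so that match is only one possibility. Nothing below depends on it.

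**Step 1, expected LOCF estimate at 4 weeks.** With a share d missing equally in each arm and unrelated to the scores, and a flat sham arm:

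LOCF difference = (1 − d) × true 4-week benefit + d × benefit in the score carried forward.

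The carried benefit is 3 points for patients last seen at week 6 and 0 for those lost before the tenth session.

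| Missing | True 4-week benefit | All last seen at week 6 | All lost before session 10 |
|---|---|---|---|
| 10% | 1 | 0.9 × 1 + 0.1 × 3 = 1.2 | 0.9 × 1 + 0.1 × 0 = 0.9 |
| 20% | 1 | 0.8 × 1 + 0.2 × 3 = 1.4 | 0.8 × 1 + 0.2 × 0 = 0.8 |
| 30% | 1 | 0.7 × 1 + 0.3 × 3 = 1.6 | 0.7 × 1 + 0.3 × 0 = 0.7 |
| 20% | 0 | 0.8 × 0 + 0.2 × 3 = 0.6 | 0 |
| 20% | 3 | 0.8 × 3 + 0.2 × 3 = 3.0 | 0.8 × 3 + 0.2 × 0 = 2.4 |

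With 20% missing, a true benefit of 1 and a fraction q of losses falling after week 6, the estimate is 0.8 + 0.6q. The bias is upward when q exceeds one third, downward below that, and zero at exactly one third. Patients last seen at week 7 carry whatever benefit exists then.

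**Step 2, error rates.** Simulation of a two-arm contrast at 4 weeks, with 15 per arm, SD 2 and correlation 0.5. For an effect that fades from 3 points to 0, with 20% missing and all last seen at week 6, the type I error is about 11% against a nominal 5%. With 10% missing it is about 6%, and with 30% about 18%. If the effect fades only to 1.5 points, the bias at 20% missing is 0.2 × 1.5 = 0.30 and coverage of the 95% interval is about 93%.

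**Step 3, standard error.** With 20% missing, no change after dropout and the week-6 score carried forward, the mean reported standard error is 0.72 and the actual sampling SD of the LOCF estimate is 0.72 to 0.73. Coverage is about 95%. Under those conditions LOCF reports its own variability correctly. The poor coverage in step 2 comes from bias.

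**The case against.** Several points on the other side have force.

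- **Standard errors.** A reader might infer that LOCF always understates uncertainty because filled-in values count as observed. Step 3 does not bear this out. The LOCF standard error is about 11% below that of an analysis of the 12 observed per arm (0.72 against 2 × √(2/12) = 0.82), but those are two different estimators, and the gap does not show that LOCF misreports its own precision. This objection stands.
- **Direction.** A reader might also infer that LOCF favours active stimulation. That needs losses concentrated after week 6 and an effect that fades. The article gives neither dropout timing nor a course after treatment, and early losses that are equal across arms already turn the bias downward. This stands too.
- **Amount of missing data.** The nine extra patients are a contingency, not a forecast, and the article describes reminders, messages and flexible hours to retain patients. Actual loss may be below 20%. That shrinks the bias in proportion but leaves the rule unchanged.
- **Stable scores.** If pain does not change after the last visit attended, LOCF is unbiased. That is correct, but the plan neither argues for stability nor tests it.

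It cannot be said that the choice is left to an unseen analysis plan: the article itself fixes LOCF.

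**Conclusion.** The point holds as a fault in a stated analysis rule. LOCF is the sole missing-data method, it is presented as if it were intention-to-treat, and it rests on an untested assumption of frozen scores in the phase meant to show whether scores change.

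Under the assumed 20% loss and 3-point end-of-treatment benefit, a true 4-week benefit of 1 point is reported as anything from 0.8 to 1.4, depending on whether patients leave before the tenth session or after week 6. A benefit that has vanished is reported as 0.6 points in the late-loss case, with type I error of about 11% if the SD is 2 and the correlation 0.5. These figures illustrate the mechanism and do not predict this trial's bias. The documents do not support a claim that the bias has a known sign, nor that standard errors are too small in general. The plan should be changed, but the fault is repairable and does not undermine the design.

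**What to change.** In the Statistical analysis section:

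1. State separately that all randomised patients are analysed in the arm to which they were allocated.
2. Replace LOCF as the primary rule with a likelihood-based (REML) linear mixed model for repeated measures on all observed scores, with group (three arms), visit and group-by-visit.
3. Keep baseline as one of the modelled visits, with a common baseline mean across arms. If baseline were only a covariate, a patient lost before week 6 would have no outcome in the model and would drop out of the analysis. Modelled as a visit, it lets every randomised patient with a baseline score contribute.
4. This model assumes data missing at random, so add a sensitivity analysis for departures from that. LOCF may stay as a further sensitivity analysis, but not as the primary rule.

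The cost is more than a change of wording. The model replaces the mixed ANOVA, and with it the Mauchly and Greenhouse-Geisser steps and partial η², which would give way to model-based differences with confidence intervals. The section would also need to say how missing scores are handled if the Kruskal-Wallis or Friedman tests are used. No new data, visits or patients are needed.

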## Discussion

This is the first methodologically designed trial to evaluate the effect of tDCS in ESRD patients undergoing HD. Up to 82% of CKD patients undergoing HD have chronic pain associated with depression, anxiety, poorer QoL, and greater limitations in daily activities [14]. Patients with CKD are prescribed a large number of medications that could promote potentially adverse effects on kidney function or complications due to decreased kidney function. Other non-pharmacological management could improve pain and functionality with no major adverse events.

tDCS is a safe, effective, low-cost, and accessible method for treatment of chronic pain syndromes and it is a potential neuromodulatory technique to relieve pain and depression and increase functionality in ESRD patients undergoing HD.

The protocol described in this paper is a randomized controlled trial designed to guide the development of a larger multicentre study to determine the safety, clinical viability, and patient acceptance of tDCS. The choice of a study design involving three sessions per week offers good conditions to use tDCS in real-world conditions. We assume that the design of the research study may not be accessible to all individuals with ESRD undergoing HD. There will be some clinical and social limitations to include patients in this trial, as it is expected that patients have low educational and income levels, and for these reasons, adherence could be impaired.

If a positive effect is demonstrated in pain, mood states, and functionality, tDCS may represent an important alternative and complementary option for non-invasive brain stimulation for ESRD patients undergoing HD.

Thus, new treatments supporting this strategy are required to improve the care of CKD patients undergoing HD suffering from chronic pain.

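### Raw partial η² is graded small, moderate or large at cut-offs that, in a 45-patient trial, an ineffective treatment will usually pass at the lowest level

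*Protocol article*

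**What the plan says.** The Statistical analysis section of the protocol article fits one model to every outcome: "The effects of stimulation on primary and secondary outcomes will be calculated using a mixed ANOVA model". Its within-patient factor is "time of treatment (baseline, tenth day, first follow-up, and second follow-up", that is, four visits. Its between-patient factor is written as "the group of stimulation (active and sham), and the interaction term time vs group".

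Partial η² is the only effect-size measure named, and it "will be calculated as measures of effect size in the ANOVA results (main effects and interaction effects". The grading follows: "where η^2^ = 0.01 will be considered small, η^2^ = 0.06 moderate, and η^2^ = 0.14 large effect". Significance is set separately at p < 0.05, and nothing makes a label depend on it.

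The Sample size section fixes the numbers: "Thus, 45 patients will be recruited and randomized into three groups of 15 patients each".

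**The concern.** Partial η² is the share of variation that the fitted effect takes up in the sample. Chance differences between arms take up some of it even when the treatment does nothing, so the statistic is never negative and its expected value under no effect is above zero. In a small trial that null value can exceed the lowest cut-off.

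The measure is also unsigned and, with three arms, omnibus. The same value arises if sham does best, or if M1 and DLPFC differ only from each other. It therefore does not estimate M1 versus sham or DLPFC versus sham, which are the contrasts behind the primary objective in the Background.

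What is at stake is how inconclusive results are described. In a trial of this size, readers lean on effect sizes when p is not significant, and that is where these labels mislead.

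**Working it through.** **The plan's own figure.** The article gives no probability for the labels. Its nearest figure is the 36 patients before the dropout allowance (α 0.05, power 95%, effect size 0.40). I take 0.40 as Cohen's f for a group-by-time interaction with four visits, sphericity and between-visit correlation ρ = 0. The article states no ρ, so that value is my assumption. Then λ = N × f² × 4.

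- Three groups, N = 36: λ = 36 × 0.16 × 4 = 23.04 on (6, 99) df, power 0.958. N = 33 gives 0.937, so 36 is the smallest balanced size.
- Two groups, same assumptions: N = 30 (λ = 19.2 on 3, 84 df) already gives 0.962, and N = 28 gives 0.948.

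The stated 36 therefore fits a three-level group factor, given ρ = 0.

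**Inputs for the labels.** 45 patients and three arms of 15 (Sample size); four visits, cut-offs 0.01 / 0.06 / 0.14 and a group factor written with two levels (Statistical analysis). Last observation carried forward keeps the analysed number near 45.

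**Formula.** Partial η² = df1·F / (df1·F + df2). With no effect, normal data and sphericity, it follows a Beta(df1/2, df2/2) distribution with mean df1 / (df1 + df2).

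**Three-level group factor**

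- Group, df (2, 42): P(≥ x) = (1 − x)^21. So 0.99^21 = 0.810, 0.94^21 = 0.273, 0.86^21 = 0.042. Mean 2/44 = 0.045.
- Time by group, df (6, 126), Beta(3, 63): P(≥ x) = (1 − x)^65 + 65x(1 − x)^64 + 2080x²(1 − x)^63. At 0.01 this is 0.520 + 0.342 + 0.110 = 0.972. At 0.06 it is 0.018 + 0.074 + 0.152 = 0.244. At 0.14 it is 0.004. Mean 6/132 = 0.045.

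The null mean is thus about four and a half times the small cut-off.

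**Both codings under no effect, N = 45**

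| Effect | df | ≥ 0.01 | ≥ 0.06 | ≥ 0.14 | null mean | partial η² needed for p < 0.05 |
|---|---|---|---|---|---|---|
| Group, 3 levels | 2, 42 | 0.810 | 0.273 | 0.042 | 0.045 | 0.133 |
| Time by group, 3 levels | 6, 126 | 0.972 | 0.244 | 0.004 | 0.045 | 0.094 |
| Group, 2 levels | 1, 43 | 0.513 | 0.105 | 0.011 | 0.023 | 0.086 |
| Time by group, 2 levels | 3, 129 | 0.729 | 0.046 | < 0.001 | 0.023 | 0.059 |

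**Labelled but not significant, no effect.** Where the cut-off lies below the value needed for significance, subtract 0.05.

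- Three levels, at least small: 0.810 − 0.05 = 0.76 (group) and 0.972 − 0.05 = 0.92 (interaction). At least moderate: 0.22 and 0.19.
- Two levels, at least small: 0.46 and 0.68. At least moderate: 0.055 for group. For the interaction it is none, because 0.06 lies just above the significance threshold of 0.059.

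**Sphericity.** Simulation of three arms of 15 at four visits (20,000 trials per setting, first-order autoregressive correlation 0 to 0.95) gave 0.95 to 0.97 for the interaction and 0.81 for group at the 0.01 cut-off.

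**Would a bias-corrected measure suffice?** Partial ε² = 1 − (1 − η²)(df1 + df2)/df2. With three levels, ε² ≥ 0.01 requires η² ≥ 1 − 0.99 × 42/44 = 0.055 (the same for 126/132). Under no effect this occurs in 30% of trials for both group and interaction. The correction brings the null mean to about zero but does not by itself stop labels on null results.

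**The case against.** The strongest reply is that the labels decide nothing. They are conventional benchmarks, the article does not say that every result must be binned, and the F test at p < 0.05 is what separates effect from no effect. Much of this stands. Type I error is untouched, and a reader who infers that the labels raise the false-positive rate would be wrong. Reading 0.01 as a lower bound is the usual reading but is not spelled out. What does not stand is that the p value neutralises the labels: nothing ties the two together, so a non-significant result can carry a size label, and under no effect it often will.

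Second, the larger percentages need a three-level group factor, while the model sentence names two. This stands as a condition. Three randomised arms and the reproduction of 36 favour three levels. On the literal wording the small label is still common, but the moderate label is not.

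Third, a reader might infer that the next trial will be undersized, because the Discussion calls this one "a randomized controlled trial designed to guide the development of a larger multicentre study". The documents do not support that step. They say the larger study concerns safety, clinical viability and patient acceptance, and nowhere that it will be sized on partial η². Nor should the probabilities be recomputed for 36 completers, given the planned carrying forward of last observations.

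Fourth, Bonferroni post-hoc comparisons are planned, and an article may leave pairwise differences with intervals to a fuller document. That is fair. Their absence is not the finding; the grading rule that the article does fix is.

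**Conclusion.** The point holds as a defect of interpretation, of minor to moderate severity. With three arms of 15, four visits, normal data and 0.01 as a lower bound, an ineffective treatment gets at least a small label in 81% (group) and 97% (time by group) of trials, and at least a moderate one in 27% and 24%. With the two-level factor as written, the figures are 51% and 73%, then 10% and 5%. Departure from sphericity lowers the 97% only to about 95%.

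The significance test is sound in this respect. What fails is the description attached to non-significant results, which would routinely be called small and, under the three-level coding, quite often moderate. The measure behind the label has no direction and does not address either active arm against sham.

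**What to change.** In the Statistical analysis section, remove the small / moderate / large grading of raw partial η². Report as effect sizes the M1-sham and DLPFC-sham mean differences at each post-treatment visit with 95% confidence intervals, adding Hedges' g if a standardised value is wanted. If a variance-explained figure is kept, use partial ω² or ε² with a confidence interval, and attach no size label when the interval includes zero. The interval condition is essential, because the bias correction alone still passes 0.01 in about 30% of null trials. In the same edit, reconcile the two-level group factor in the model with the three randomised arms.

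The cost is a sentence or two of text and a little post-processing, since ω² and ε² come from the same ANOVA table. No new data are needed. Variance-explained figures will be slightly smaller than raw partial η².

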### Adverse event monitoring and adherence

To date, the use of conventional tDCS protocols in human trials (20 min, 2 mA, and ten sessions, in the case of this trial) has not produced any reports of serious adverse effects or irreversible injury [24]. Adverse events will be carefully monitored during all steps of the study by asking patients, after each session of stimulation and during the follow-up period, whether they had experienced any adverse events, and the relationship of these events to treatment with tDCS. The most commonly reported minor adverse events include the sensation of tingling or discomfort under the electrode sites, reported in both active and sham conditions [24, 25]. These events include participant ratings of frequency, severity, importance, and associated distress. To evaluate the adverse effects, we will record any musculoskeletal symptoms such as pain and fatigue, itching, tingling, headache, burning, discomfort, or cardiovascular symptoms such as shortness of breath, chest pain, and abnormal increase in blood pressure. Participants will receive care as appropriate for any harm that arises as a result of study participation.

A doctor will be on duty during tDCS sessions to handle any adverse events, including problems with dialysis. The researchers will communicate any important protocol modifications to relevant parties.

The main strategy to improve adherence of patients is to perform tDCS during HD sessions and explain to participants the relevant contribution to the treatment of chronic pain, including the possibility of improving pain. There will also be flexible hours offered for receiving therapy according to the HD, as well as direct contact by telephone with participants confirming the evaluation dates and reinforcing treatment adherence.

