## Background

A complete physical and mood assessment is critical to provide an appropriate treatment plan for chronic kidney disease (CKD) [1]. Management of persistent pain in this population requires an adequate understanding of the pathogenesis and clinical conditions with the aim of improving life span and quality of life (QoL) [2]. Up to 82% of CKD patients undergoing hemodialysis (HD) experience chronic pain, and 35–70% of patients describe the pain as moderate to severe [1–3]. Chronic pain in CKD patients undergoing HD may be caused by various factors, including musculoskeletal, ischemic, abdominal, chest, and neuropathic pain [2, 3].

Chronic pain in CKD patients has been considered a genuine neurologic disturbance, and it co-occurs generally with many pain syndromes in the context of suffering throughout the lifetime [4, 5]. Studies suggest that long-term chronic pain may result in the development of adaptive neuroplasticity and functional reorganization, with a network shift from affective processing of salience to cognitive modulation of pain [6]. Pain-related regions are parts of the pain neuromatrix (medial prefrontal cortex, posterior cingulate cortex, and insula) and exhibit abnormal functional and structural changes in chronic pain when compared with those in healthy people [6]. These modulatory system regions are associated with chronic pain, cognitive control of emotion, and self-referential processing [6].

Pain is a major cause of depression, disturbed sleep patterns, impaired dialysis adequacy (if unable to endure full sessions), and likeliness of withdrawal from dialysis [3]. Several researchers have also shown that pain negatively impacts many aspects of QoL, including physical function, social function, daily activities, energy, fatigue, and emotional function [7]. Markers of both muscle mass and strength are important predictors of outcomes in this patient population and a decrease in these markers can contribute to risk of physical disability and cognitive decline [8].

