### Inclusion criteria

Patients will be included if they fulfill the following inclusion criteria: (1) male or female aged 18 to 75 years; (2) undergoing HD with ESRD (CKD 5D^2^) for > 3 months, (4-h session); (3) pain related with a score of more than 4 (range of scores from 1 to 10) in a visual analog scale (VAS) for > 3 months; (4) have physical capacity to do physical evaluation and be capable of consenting to treatment and understanding study explanations and questionnaires; and (5) provide informed consent.

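### The adverse-event checklist includes pain, which every patient must have at entry, but is described only after stimulation, so comparison with sham is diluted and the pain item is mixed with efficacy

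*Protocol article*

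**What the plan says.** In the Protocol article, the section Adverse event monitoring and adherence fixes the content of the record: "we will record any musculoskeletal symptoms such as pain and fatigue, itching, tingling, headache, burning, discomfort, or cardiovascular symptoms", the last group being described as "such as shortness of breath, chest pain, and abnormal increase in blood pressure". It fixes the timing and source too: events are sought "by asking patients, after each session of stimulation and during the follow-up period, whether they had experienced any adverse events", and patients are also asked about the link to stimulation. Participants rate frequency, severity, importance and distress. Nothing in the section limits recording to symptoms that are new or worse.

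The Inclusion criteria admit only patients with "pain related with a score of more than 4 (range of scores from 1 to 10) in a visual analog scale (VAS) for > 3", the duration being in months. The Background names the possible sources of chronic pain in this population, "including musculoskeletal, ischemic, abdominal, chest, and neuropathic pain", and says that "pain negatively impacts many aspects of QoL, including physical function, social function, daily activities, energy, fatigue, and emotional function". It gives no rates for chest pain or fatigue, and neither is an entry criterion.

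Under Outcome measures, pain by VAS and McGill Pain Questionnaire (MPQ) is the primary endpoint. It is assessed at week 2 (baseline), at week 6 after the tenth session, and at weeks 7 and 10. The VAS asks about the last 24 hours.

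**The concern.** The complaint that qualifies a patient for the trial is also on the list of adverse effects. Recording *any* such symptom after a session, with no matching record from before it, cannot show whether stimulation produced the symptom or the patient arrived with it. Later analysis cannot restore a reference that was never collected.

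Two consequences follow. Symptoms already present reduce the contrast between active and sham, in a trial with only 15 patients per arm. And for pain, the adverse-event record and the primary endpoint measure much the same thing, so benefit and harm pull one item in opposite directions. The abstract's Discussion promises initial evidence on safety as well as efficacy, and the main Discussion says the trial should guide a larger multicentre study, so the safety record is meant to be used.

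**Working it through.** The plan states no figure on this point, so there is none to reproduce. The check sets the passages side by side and then illustrates the size.

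**1. Is there a usable reference?** Baseline VAS and MPQ are taken at week 2 and next at week 6, with all ten sessions between the two. They give a pain level before treatment but none before each session. They are not described as covering fatigue, itching, tingling, burning or shortness of breath. Comorbidities are collected, but these are diagnoses and not symptom levels. The severity ratings grade a symptom without showing that it is new.

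**2. Dilution.** Let *b* be the share of patients in whom the symptom is recorded from background causes, equal in all arms by randomisation. Let *e* be the share of patients without it in whom tDCS causes it. Then:

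- sham = b
- active = b + (1 − b)e
- expected difference = (1 − b)e

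The arm size of 15 is from the Sample size section. The value e = 0.30 and the range of b are assumptions; the article gives neither. Power uses the two-sided 5% normal approximation, Φ[(d − 1.96·se0)/se1], where d is the difference, se0 the pooled standard error and se1 the unpooled one. For b = 0.40 and 15 against 15:

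- active = 0.40 + 0.60 × 0.30 = 0.58, so d = 0.18
- pooled share 0.49; se0 = √(0.49 × 0.51 × 2/15) = 0.1825
- se1 = √[(0.40 × 0.60 + 0.58 × 0.42)/15] = 0.1796
- power = Φ[(0.18 − 0.3578)/0.1796] = Φ(−0.99) = 0.16

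| Background b | Active | Difference (points) | Power, 15 v 15 | Power, 15 sham v 30 active |
|---|---|---|---|---|
| 5% | 33.5% | 28.5 | 0.51 | 0.58 |
| 20% | 44% | 24 | 0.28 | 0.34 |
| 40% | 58% | 18 | 0.16 | 0.20 |
| 60% | 72% | 12 | 0.10 | 0.13 |
| 80% | 86% | 6 | 0.06 | 0.08 |
| 95% | 96.5% | 1.5 | 0.04 | 0.05 |

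The approximation is rough at this sample size, most of all in the last row, but the direction is clear. With e = 0 and no effect on background, the expected difference is 0 at every b. Background symptoms alone hide harm; they do not create a false signal of it.

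**3. The pain item.** Step 2 assumes that tDCS leaves the background unchanged. For pain the trial expects otherwise: the Sample size section cites a mean fall of 3 VAS points under active stimulation and no improvement under sham. If relief lowers the background share in an active arm from b to a, the difference becomes a + (1 − a)e − b. This is negative whenever b − a exceeds (1 − a)e. With assumed values b = 0.80, a = 0.60 and e = 0.30, the active arm records 0.60 + 0.40 × 0.30 = 0.72 against 0.80 in sham. That is 8 points fewer, although 12 points of the active figure are caused by stimulation. Without relief the difference would have been +6 points.

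A patient who enters just above 4 and improves by 3 still has some pain. A plain yes/no count may therefore stay near its ceiling, and the relief would show in the severity ratings instead. The item either says little or is mixed with efficacy.

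**The case against.** The strongest reply is that the trial is randomised, with a sham arm and blinded patients and assessors. Background symptoms are expected equally in all arms, so harm can be compared between arms without judging the cause of any single event. The article names symptoms separately and specifies no pooled count, so extra burning or tingling under active stimulation would show in its own row. This stands. A reader might infer that harm from tDCS cannot be isolated at all; the documents do not support that. The reply does not cover the loss of sensitivity in step 2, nor step 3, where the imbalance arises after treatment starts and randomisation does not remove it.

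A reader might also infer that fatigue and chest pain are present in all patients at entry. Only pain is shown to be; the other two are named as possibilities, without rates. Nor is it shown that the patient alone decides causality. Patients are asked "whether they had experienced any adverse events, and the relationship of these events to treatment with tDCS", but that does not exclude an investigator's judgement. Similarly, the text says blood pressure will be recorded and does not say that it rests on patient report.

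Finally, a journal article may leave a definition of new or worsened events to the full protocol, and the schedule figure is not shown. That is a fair caution. The point rests, however, on what the article does state: the content of the list, its timing, and an entry criterion that overlaps with it.

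**Conclusion.** The point holds in a limited form, as a cheap improvement. As described, the checklist does not separate new or worsened symptoms from those present before stimulation, and for pain this affects every patient. The cost is lost sensitivity for symptoms already common in the population, plus a pain item whose comparison with sham is confounded with the primary outcome, in the direction of apparent safety if tDCS works. Under the assumed 30% causal rate, power with 15 per arm falls from about one half at 5% background to near the significance level at 80% or more. The true background and causal rates are not in the article, so these figures show the pattern and are not estimates for this trial. The comparison by symptom remains informative for effects that are rare without stimulation.

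**What to change.** Give the same symptom checklist, with its severity rating, before the first session and before each later one. Count a symptom as an adverse event only if it is new or worse than the pre-session record. Keep the record from before the first session as the reference for follow-up and for effects that build up over sessions. Tabulate events by symptom and by arm (M1, DLPFC, sham), whatever cause is assigned. Report worsening of the presenting pain separately from all other events.

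The cost is about one extra column on the per-session form and a minute or so per session. Patients are already seen and questioned each time, so no extra visits are needed.
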